***6.2.2. Additional Secondary Objectives***

• To test the hypothesis that atomoxetine improves symptoms of ADHD compared to placebo after 12 weeks of treatment on the mean change from baseline to endpoint as measured by:

− Clinical Global Impression-ADHD-Severity (CGI-ADHD-S)

− CAARS Self Report (CAARS-S:SV)

− Patient Global Impression – Improvement (PGI-I)

• Montgomery Asberg Depression Rating Scale (MADRS): To assess the effect of atomoxetine in treating symptoms of depression in adults with ADHD as measured by the mean change in the total score after 12 weeks of treatment.

• Beck Anxiety Inventory (BAI): To assess the effect of atomoxetine in treating symptoms of anxiety in adults with ADHD as measured by the mean change in the total score after 12 weeks of treatment.

• To assess the correlation between the improvements on the AAQOL-29 Total Score with symptom reduction as measured by improvement on the CAARS- Inv:SV total ADHD symptom score.

***6.2.3. Secondary Functional Outcome Objectives***

• To test the effect of atomoxetine for the following measures compared to placebo:

− Habits Timeline Followback (TLFB) (Alcohol, Nicotine, Caffeine, Marijuana, and Drugs): the incidence of use for each of the following habits separately: alcohol, nicotine, caffeine, marijuana, and drugs as measured by the mean change

− Fagerstrom Test for Nicotine Dependence

− Social Adaptation Self-Evaluation Scale (SASS)

− Driving Behavior Survey Self-Report

− Driving Behavior Survey - Other Report

− Behavior Rating Inventory of Executive Function-Adult Version Self

Report (BRIEF-A)

− Epworth Sleepiness Scale

• To assess baseline smoking status as a predictor of response (a 25% decrease from baseline on the CAARS-Inv:SV total ADHD symptom score) and strong response (a 40% decrease from baseline on the CAARS-Inv:SV total ADHD symptom score ) to atomoxetine treatment compared with placebo.

**7. Investigational Plan**

**7.1. Summary of Study Design**

Study B4Z-US-LYDZ(b) is a multi-center, 12-week, randomized, placebo-controlled, double-blind, trial with 3 study periods for the evaluation of safety and efficacy between atomoxetine and placebo in approximately 440 adult patients (age 18 to 30) with ADHD at approximately 35 sites in the United States and Puerto Rico.

The study design employs a blinded, randomized placebo lead-in to blind patients and investigators to the start of active therapy (see discussion on the rationale for this design in Section 7.2). This protocol contains a description of the blinded study design with sufficient information to ensure patient safety. There will be no circumstances under which investigators or site personnel will know the complete details of the study design. A separate document (IRB Supplement 1) contains a complete account of the study design. IRB Supplement 1 will be provided along with this protocol to investigators’ ethical review boards and to regulatory agencies for review.

The protocol design contains a community sample (CS) which is a superset of subjects who do not qualify or qualify but choose not to participate in the randomized research clinical trial (RCT). Non-interventional health outcomes data will be collected from CS participant via web-based self-reporting done through the study website. The participants of the CS will interface only with the study website and will be independent of the RCT and investigator trial sites. The CS is further described in Protocol Attachment LYDZ(b).5.

**Pre-Screening Period**

**Study Period I Screening**

**Study Period II**

**12 weeks**

**Study Period III**

**12 weeks**

Outpatient Site

Screening

Passed screen, site available, & willing to participate in research clinical trial

**ALL SUBJECTS Web-based ADHD**

**& Study Screen**

**Atomoxetine 40-100mg** *(Dosed BID)*

**Placebo**

Randomization and transition to active study drug for ATX group will occur between Visit 2 and 4

**Patients completing SPII Atomoxetine OPEN-LABEL**

**36-100mg (***Dosed QD or BID)*

**Community Sample***

**Visit: 1 2 4 6 9**

*****Community Sample** includes only subjects who:

▪ Meet ADHD criteria and meet Incl/Excl screen, & willing to participate in research clinical trial, NO site available

▪ Meet ADHD criteria and Incl/Excl screen but opt out of research clinical trial

▪ Meet ADHD criteria but fails Incl/Excl Screen

ATX = Atomoxetine

**Figure LYDZ(b).1. Illustration of study design of B4Z-US-LYDZ(b)**

This study utilizes web-based screening assessments, web-based informed consent documents (electronic signature), and web-based patient-rated scales (e-PROs) for both the RCT and CS.

**Study Period I:** A screening period of 5 to 28 days to determine eligibility for the double-blind acute treatment phase.

Web Screening**:** Subjects interested in participating in the study will be evaluated through the following web-based screening process:

• The website will require the subject to opt-in (opt-in is a form of consent) prior to completing the first level of screening which is to determine the likelihood of meeting ADHD diagnostic criteria.

o Recruitment of subjects may occur through a variety of methods that include but are not limited to: centralized advertising which will direct subjects to the website, ADHD databases, investigator databases, or local (investigator level) advertising. Subjects recruited from investigator databases or site- level advertising will also be directed to the study website as the “first-step” of screening for the study.

• Subjects will complete an internet-based non-identifiable Adult ADHD Self- Report Scale (ASRS) to determine the likelihood of meeting ADHD diagnostic criteria. A raw score of 14 or greater (screen positive) is required for the subject to be eligible to proceed to the next level of screening.

• If the subject  **screens positive** for the web-based ASRS criteria for ADHD:

o The website will require the subject to opt-in prior to answering additional inclusion/exclusion criteria questions via the study website. After the subject opts-in, the subject is then presented with questions to answer regarding

other **study inclusion/exclusion criteria** (including the Patient Health Questionnaire) to determine if the subject meets eligibility to proceed with further evaluation for the RCT by a clinical trial site.

o Subjects who meet other inclusion/exclusion trial criteria AND for whom a site is available in their geography will be eligible to enter the RCT.

o Subjects deemed eligible for the RCT will be presented with site contact information for the investigator(s) participating in their region. Additionally, with subject permission, contact information for subjects eligible for the

RCT will be provided to sites within the geography of the eligible subject. That site will contact the eligible subject to schedule further evaluation (labs, etc) by the clinical trial site to determine if the subject fully meets all study inclusion/exclusion criteria.

• Subjects who  **screen positive** for the ASRS criteria for ADHD but  **do not qualify**

for the RCT for the following reasons:

o Do not meet full inclusion/exclusion criteria for the RCT (as determined by the web-based inclusion/exclusion questionnaire),

o Meet full inclusion/exclusion criteria per the web-based screening but do not have a site located within their geography, OR

o Meet full inclusion/exclusion criteria for the RCT per the web-based screening but do not wish to participate in the RCT,

***will be eligible to participate in the CS*** (described in Protocol Attachment LYDZ(b).5). Subjects participating in the CS interface only with the study website and are independent of the investigator clinical trial site.

RCT Site Screening**:** At or before Visit 1, informed consent for the RCT will be obtained by the investigator site before any study procedures are conducted and before patients discontinue any excluded medications. An informed consent document (ICD) approved by an ERB or similar body will be signed by the patient and/or representative deemed appropriate according to local laws and regulations. Information from assessment questionnaires and medical history will be recorded in the source documents and/or in the electronic data capture system. Patients will undergo laboratory tests, an ECG

evaluation, a psychiatric evaluation, and a physical examination with a patient history being recorded. Protocol Attachment LYDZ(b).1 contains a complete list of assessment procedures. Clinical assessments conducted during the screening period will include clinical history, Structured Clinical Interview for DSM-IV Axis Disorders-Research Version (SCID-RV; First et al, 2000), and the Adult ADHD Clinician Diagnostic Scale version 1.2 (ACDS v1.2). The CAARS-Inv:SV will also be administered and if the patient’s CAARS-Inv-SV total ADHD symptom score decreases more than 25% between Visit 1  **and** Visit 2, the patient will be discontinued. **Note:** The MADRS will also be administered and a *baseline* score of 3 or greater on Item 10 (Suicidal Thought) of the MADRS is an automatic exclusion from the trial. Exclusion item number [20] outlines details regarding Item 10 of the MADRS administered post-baseline.

If necessary for scheduling or other reasons, the tasks for Visit 1 can be accomplished on

2 separate clinic days. In this case, the date of the visit will be the first of the 2 clinic days and the 2 clinic days must not be separated by more than 14 days. However, if washout of an excluded medication is required, the clinic days can be separated by the time required for appropriate washout of the medication. If the time between Visit 1 and Visit 2 exceeds the visit window interval to allow for washout of medications, this will not be considered a protocol violation.

**Washout.** For patients who have been taking medications excluded by this protocol, the following guidelines for medication washout will apply.

(Special note: informed consent must be obtained prior to beginning any medication washout-even if the washout is commenced prior to Visit 1).

• If the patient is on medication requiring washout on the first day of Visit 1, the ECG and laboratory examinations should be obtained on the second clinic day of Visit 1. The patient must be medication-free for at least 5 half-lives of the drug. The first clinic day will be considered the Visit 1 date.

• Patients who enter the study at Visit 1 taking stimulant medications for the treatment of ADHD must be medication-free for at least 24 hours immediately prior to Visit 2 before diagnostic baseline data/measures are obtained. These medications will also need to be discontinued for the duration of the trial.

• Patients who are taking any medication excluded by the protocol at Visit 1 that has a half-life of >24 hours must have a washout equal to or greater than 5 half- lives of the parent compound and any active metabolite of the parent compound immediately prior to Visit 2.

• Patients who are taking SSRIs at Visit 1 must have a washout equal to or greater than 5 half-lives of the parent compound and any active metabolite of the parent compound  **or** for 2 weeks, whichever is  **longer**, immediately prior to Visit 2.

• Patients who are taking any psychotropic medications that have a parent and/or active metabolite half-life requiring > 28 days of washout must have their medications reviewed by the Eli Lilly and Company research physician who is responsible for monitoring the study.

• Patients who are taking any health food supplements that, in the investigator’s opinion, may have central nervous system activity (for example, St. John’s Wort, melatonin, etc.) must have a washout equal to a minimum of 5 half-lives of that supplement immediately prior to Visit 2. If the half-life of the supplement is unknown, then the patient should have a 28-day washout.

At Visit 2, patients will be further evaluated for inclusion/exclusion criteria and, patients meeting requirements will be “enrolled” in the study and receive study therapy. Patients who do not meet all entry criteria at Visit 2 will be discontinued from the study.

**Note**: *patients who do not meet criteria for the RCT after screening at an investigative site (screen failure) are* ***not*** *eligible for the CS described in Protocol Attachment LYDZ(b).5.*

**Study Period II:** A 12-week acute phase of double-blind treatment. Patients will be assessed 2 weeks after Visit 2 and then every 3 weeks until Visit 5 then at 4 weeks (Visit

6, the end of acute phase of study). Patients who meet all screening criteria will be

dispensed blinded medication and instructed to begin doses the morning following Visit

2. Patients will be randomized 1:1 to either atomoxetine or placebo some time between

Visit 2 and 4. Since the time at which randomization occurs is double-blinded, neither

the investigator nor the patient will know when randomization occurs. Further, because of the potential for a double-blind placebo lead-in, any patient randomly assigned to atomoxetine may receive placebo some time during the potential lead-in phase. Patients in the atomoxetine group may receive atomoxetine as early as Visit 2 or as late as Visit 4. The study drug is to be taken by the patient twice-daily, once in the morning and once in the afternoon or early evening. It is strongly recommended to take the study medication with food. Patients randomized to atomoxetine will begin treatment with 40 mg/day (dosed 20 mg twice daily [BID]) for a minimum of 7 days. Immediately following the last dose of 40 mg/day (dosed 20 mg BID), the patient will receive 80 mg/day (dosed 40 mg BID) atomoxetine for a minimum of 7 days. Following Visit 3, one unscheduled

dose decrease is allowed if needed for tolerability or safety. Only one dose decrease will

be permitted during Study Period II.

Starting at Visit 5, if in the judgment of the investigator, the patient has significant residual symptoms, the dose can be increased to the maximum dose of 100 mg/day (dosed 50 mg BID). However, patients who previously required a dose decrease due to safety or tolerability will not be permitted to have a dose increase.

The unscheduled dose decrease or dose increase will only be allowed by one dose level (that is, 80 mg/day to 40 mg/day, 100 mg/day to 80 mg/day, or 80 mg/day to 100 mg/day). Patients unable to tolerate 40 mg/day (dosed 20 mg BID) should be discontinued. Efficacy data and health outcome measures as outlined in the schedule of events will be evaluated.

If the patient has access to the internet, the patient-rated scales (electronic patient- reported outcomes [e-PROS]) may be completed by the patient outside of the investigator’s office. The patient will be permitted to log into the study website 3 days prior to the originally scheduled visit to begin completing patient-rated questionnaires. The patient may log in and out of the study website without losing any data captured at

the previous login session. If the patient has not completed all of the patient-rated scales on the day of the originally scheduled clinic visit, the patient must complete them at the investigator’s site by the end of the clinic visit. If the patient reschedules the clinic visit, the rescheduled date must occur within the visit interval described in Protocol Attachment LYDZ(b).1. The patient will still be permitted to complete the e-PROs prior to the rescheduled clinic visit IF the visit is within the visit interval window.

**Study Period III:** A 12-week open-label extension period. Patients completing Study Period II will be eligible to enter Study Period III. Patients will be administered open- label atomoxetine at doses of 36 to 100 mg/day that can be taken as QD or BID dosing starting the day after Visit 6.

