**Protocol Attachment LYDZ(b).1.**

**Study Schedule**

**Study Schedule, Protocol B4Z-US-LYDZ(b)**

| **Study Period** | **I** | | **II** | | | | **III** | | |
| --- | --- | --- | --- | --- | --- | --- | --- | --- | --- |
| **Visit** | **1** | **2** | **3** | **4** | **5** | **6**  **SUM IIa** | **7** | **8** | **9**  **SUM IIIa** |
| **Weeks Until Next Visit:** | **1** | **2** | **3** | **3** | **4** | **2** | **5** | **5** | **N/A** |
| **Interval Between Visits and**  **Target ( )** | **5-28 (7)** | **10-18 (14)** | **17-25 (21)** | **17-25 (21)** | **25-31 (28)** | **10-18 (14)** | **28-38 (35)** | **28-38 (35)** | **-** |
| Informed consentb | X |  |  |  |  |  |  |  |  |
| Patient number assigned | X |  |  |  |  |  |  |  |  |
| Inclusion/exclusion criteria  (including PHQ-9) | X |  |  |  |  |  |  |  |  |
| Presenting/preexisting conditionsc | X |  |  |  |  |  |  |  |  |
| Medical/psychiatric history | X |  |  |  |  |  |  |  |  |
| Physical Exam | X |  |  |  |  |  |  |  |  |
| Height | X |  |  |  |  |  |  |  |  |
| Weight | X | X | X | X | X | X | X | X | X |
| Vital signs | X | X | X | X | X | X | X | X | X |
| Demographics | X |  |  |  |  |  |  |  |  |
| Social Demographics | X |  |  |  |  |  |  |  |  |
| Previous drug therapy- ADHD | X |  |  |  |  |  |  |  |  |
| Previous drug therapy- all other  CNS Therapies | X |  |  |  |  |  |  |  |  |
| Concomitant medications | X | X | X | X | X | X | X | X | X |
| Adverse events | X | X | X | X | X | X | X | X | X |
| Dispense drug |  | X | X | X | X | X | X | X |  |
| Study drug compliance |  |  | X | X | X | X | X | X | X |
| **Investigator-Administered Scales:** | | | | | | | | | |
| ASRS (prior to v1 via web) | X |  |  |  |  |  |  |  |  |
| SCID-RV | X |  |  |  |  |  |  |  |  |
| ACDS v1.2 | X |  |  |  |  |  |  |  |  |
| CAARS-Inv-SV | X | X | X | X | X | X | X | X | X |
| CGI-ADHD-S | X | X | X | X | X | X | X | X | X |
| MADRS | X |  |  | X |  | X |  |  | X |
| **Patient-Rated Scales: d** | | | | | | | | | |
| AAQOL-29 |  | X | X | X | X | X |  |  | X |
| CAARS-S:SV | X | X | X | X | X | X | X | X | X |
| PGI-I |  |  | X | X | X | X |  |  | X |
| Habits Timeline Followback: (Alcohol, Nicotine, Caffeine, Marijuana, and Drug) |  | X | X | X | X | X |  |  | X |
| Fagerstrom Test for Nicotine  Dependence |  | X |  | X |  | X |  |  | X |
| SASS |  | X |  | X |  | X |  |  |  |
| Driving Behavior Survey - Self  Report |  | X |  | X |  | X |  |  |  |

|  |  | |  | | | |  | | |

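### No structured suicidality rating is required between medication washout and the first study dose: for an SSRI patient rated on the first Visit 1 clinic day, the automatic MADRS Item 10 exclusion rests on a pre-washout score at least 15 days old

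*Protocol*

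**What the plan says.** **The rule.** Protocol Section 7.1 (Study Period I) says that a baseline "score of 3 or greater on Item 10 (Suicidal Thought) of the MADRS is an automatic exclusion from the trial". Exclusion Criterion [20] and Section 10.1.2.5 repeat it.

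**When suicidality is rated.** Attachment LYDZ(b).1 marks the MADRS at Visits 1, 4, 6 and 9. The PHQ-9 appears only within the eligibility row ("including PHQ-9) | X"), which is marked at Visit 1 alone. The Columbia scale has no scheduled visit. Under [20] and Section 10.1.2.5.1 it follows a spontaneous report, or an Item 10 score of 2 or more at Visit 4, 6 or 9.

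**Washout.** Antidepressants are prohibited (Attachment LYDZ(b).3). Section 7.1 sets the SSRI rule: "Patients who are taking SSRIs at Visit 1 must have a washout equal to or greater than 5 half-lives", or 2 weeks if that is longer, running right up to Visit 2. For CNS-active supplements, "If the half-life of the supplement is unknown, then the patient should have a 28-day washout". Psychotropics needing more than 28 days of washout go to the sponsor's physician for review.

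**Split Visit 1.** Section 7.1 lets Visit 1 occupy two clinic days; "if washout of an excluded medication is required, the clinic days can be separated by the time required for appropriate washout of the medication". For a patient still on such a medication on the first day, "the ECG and laboratory examinations should be obtained on the second clinic day of Visit 1". The MADRS is not named there. Washout may also begin, after consent, before Visit 1. The delay has no upper limit: "If the time between Visit 1 and Visit 2 exceeds the visit window interval to allow for washout of medications", no violation is recorded.

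**Dosing.** Eligible patients are "dispensed blinded medication and instructed to begin doses the morning following Visit" 2.

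**The concern.** The sponsor chose a numeric, automatic safety exclusion, which is meant not to depend on anyone's impression. For a patient taken off an antidepressant in order to enter the trial, the period in which suicidal thinking could change lies between stopping the drug and starting study treatment. If the only pre-dose Item 10 score comes before that period, the rule describes a state that may no longer hold.

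A patient who scored 0 to 2 while on an SSRI and would score 3 or more after withdrawal could be enrolled without the cut-off being tested again. The first study doses may also be placebo, because patients assigned to atomoxetine can start it anywhere from Visit 2 to Visit 4 (Section 7.1, Study Period II).

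This is a patient-safety matter. The gap arises before treatment and is the same for both arms. It implies no bias in the comparison and no effect on the CAARS-Inv:SV analysis.

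**Working it through.** The protocol gives no figure for the age of the score, so there is none to reproduce. The check is calendar arithmetic plus a comparison of the relevant provisions.

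**Inputs**
- Pre-dose MADRS: Visit 1 only (Attachment LYDZ(b).1).
- Minimum SSRI washout ending at Visit 2: 14 days, longer if 5 half-lives exceed that (Section 7.1, Washout).
- Supplement of unknown half-life: 28 days (same place).
- Psychotropic with long washout: more than 28 days (same place).
- First study dose: 1 day after Visit 2 (Section 7.1, Study Period II).
- Visit 2 to Visit 3: target 14 days, window 10 to 18. Visit 3 to Visit 4: target 21 days, window 17 to 25 (Attachment LYDZ(b).1).

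**Age of the score at first dose, for a patient rated on the first clinic day while still taking the product**

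Age = minimum washout before Visit 2 + 1 day.

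| Product at Visit 1 | Calculation | Age at first dose |
| --- | --- | --- |
| SSRI | 14 + 1 | at least 15 days |
| CNS-active supplement, half-life unknown | 28 + 1 | at least 29 days |
| Psychotropic needing more than 28 days | more than 28 + 1 | more than 29 days |
| Any, if Item 10 is rated at Visit 2 | 0 + 1 | 1 day |

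At the Visit 2 enrollment decision itself, the SSRI score is at least 14 days old.

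**Time to the next scheduled rating**
- Visit 2 to Visit 4 on target: 14 + 21 = 35 days. Window: 10 + 17 = 27 to 18 + 25 = 43 days.
- From the pre-washout score to Visit 4 for an SSRI patient: at least 14 + 27 = 41 days, or 14 + 35 = 49 days or more on target intervals.

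**Does any other provision require a post-washout rating?**
1. *Second clinic day of Visit 1.* It may be used for the MADRS, but only the ECG and laboratory tests are directed to it. The protocol permits a post-washout score and does not require one.
2. *Visit 2 eligibility check.* Section 7.1 requires one, but no suicidality scale is scheduled at Visit 2.
3. *Columbia scale.* The score trigger operates only at Visits 4, 6 and 9. The other trigger needs the patient to volunteer the information.
4. *General baseline definition (Section 12.2.1).* It takes the latest value before active drug. With no MADRS scheduled between Visit 1 and Visit 4, it brings in no scheduled post-washout rating before first dose.
5. *Comparison within the protocol.* Inclusion [3] applies the CGI-ADHD-S threshold at both Visit 1 and Visit 2. The Item 10 rule has no such wording.

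**The case against.** The strongest reply is that the protocol already removes a patient who becomes suicidal during washout. Section 8.3.1 requires discontinuation when any of [11] to [32] appears after entry, promptly for a safety criterion, and Section 8.2.1 places [20] among the safety criteria. Entry means a recorded Visit 1, so this covers the washout interval. Section 8 requires patients to remain free of exclusions through Visit 2. Criterion [20] begins with clinical judgment of serious suicidal risk, so the MADRS cut-off is an added floor and not the only barrier. Visit 2 also involves real clinician contact: the CAARS-Inv:SV interview, the CGI-ADHD-S and adverse event recording. A washout patient is directed to a second clinic day as well.

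The exposed group is also narrow. Exclusion [16] removes major depressive disorder, panic disorder, post-traumatic stress disorder and eating disorders within the past year, and lifetime bipolar disorder, obsessive-compulsive disorder and psychosis. Exclusion [22] removes regular psychotropic users who do not stop. Screening includes a psychiatric evaluation and the SCID-RV.

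Most of this stands as mitigation, and it limits the weight of the point. It does not close the gap. Discontinuation under Section 8.3.1 depends on the criterion being observed, and without a rating the Item 10 threshold cannot be observed. Nor is the group empty. Inclusion [1] admits generalized anxiety disorder, social anxiety disorder and dysthymia diagnosed more than 2 years earlier. The protocol writes a dedicated SSRI washout rule, and Section 7.2 names fluoxetine when explaining the length of screening.

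Two further criticisms are fair. The CGI-ADHD-S rule is a severity criterion, so it serves only as a model for wording and sets no safety standard. The supplement and long-washout figures add little, since the protocol gives no reason to expect suicidality on stopping a supplement and the long-washout case already goes to sponsor review. The SSRI case carries the argument.

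**Conclusion.** The point holds as a worthwhile, inexpensive safety improvement. No statement in the protocol is wrong or contradictory; the schedule leaves unapplied, after washout, a rule that the protocol calls automatic. For a patient on an SSRI whose MADRS is done on the first Visit 1 clinic day, the Item 10 score governing exclusion is taken on the drug and is at least 15 days old at first study dose. It can be older, with no stated ceiling.

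This rests on two conditions: the patient is still taking the SSRI when rated, and the site does not use the post-washout clinic day for the MADRS. It does not apply where washout was completed before the rating. The protocol does not give the number of patients affected, and none is estimated here.

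**What to change.** In Attachment LYDZ(b).1, add the MADRS, or at least Item 10, at Visit 2 before drug is dispensed. The minimum would be to require it for patients who washed out a psychotropic. In Section 7.1 and Exclusion [20], state that a score of 3 or more excludes at either Visit 1 or Visit 2. The threshold and the post-baseline Columbia algorithm stay as they are.

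The score would then be 1 day old at first dose instead of at least 15. The cost is one item, or one 10-item investigator-rated scale, at a visit where investigator-rated scales are already done, plus the wording changes. The downside is a few minutes per patient and possibly a few more screen failures.
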